### Collection, preparation and archiving of biological samples

All biological samples (blood, urine, stool, breath, duodenal aspirates and endoscopic biopsies) are collected, prepared and preserved (see online supplementary file 2) as per the standard operating procedures (SOPs) prepared for this protocol.

Breath samples are being collected for testing of small intestinal bacterial overgrowth (SIBO). The first SIBO test is performed before the nutrition intervention and a second SIBO test is done 1–2 weeks prior to the endoscopy, so that findings from the endoscopy can be compared with results obtained from the hydrogen breath tests. QuinTron Breath tracker machine and associated QuinTron accessories are used for sample collection and analysis.^11^

Faecal samples are collected and cryopreserved within 20 min of production. At the site of collection, samples are aliquoted into sterile, prelabelled 2 mL cryophials and immediately placed into precharged liquid nitrogen dry cryo-shippers for transport back to the laboratory where they are transferred into a −80°C freezer prior to shipping. No additives, preservatives or media is added to the faecal samples. Culture-independent as well as culture-based analyses of the faecal microbiota (microbial community samples obtained from the UGI tract at the time of endoscopy) will be performed at Washington University in St. Louis, USA.

All other samples for biomarker assessment are carried to the laboratory using cool box and cool packs. For blood samples, with all aseptic precautions 5 mL venous blood is collected in a blood collection tube (S-Monovette 7.5 mL, Sarstedt) and transported to laboratory. Initially, 0.5 mL blood is transferred into a centrifuge tube and the remaining 4.5 mL is centrifuged for the separation of plasma. The plasma is then aliquoted and stored at −80°C. Chlorhexidine is added to urine samples as a preservative. All the samples from each individual are collected within a 3–4 days window period.

### Biomarkers

A wide array of biomarkers of enteropathy will be tested in the BEED study. A list of candidate biomarkers was prepared after a thorough literature review and analysis of data emanating from the Etiology, Risk Factors and Interactions of Enteric Infections and Malnutrition and the Consequences for Child Health and Development (MAL-ED)^12–14^ and Performance of Rotavirus and Oral Polio Vaccines in Developing Countries (PROVIDE)^15^ studies (table 2).

**Table 2 T2:** Summary table for non-invasive biomarker candidates and related processes

Process of gut health	Biospecimen	Non-invasive biomarkers
Epithelial health and repair	Faeces	Reg1B
Intestinal barrier dysfunction and bacterial translocation	Blood and urine	Alpha-1-antitrypsin, lactulose/rhamnose ratio
Intestinal inflammation	Faeces	Myeloperoxidase, neopterin, calprotectin
Systemic inflammation	Blood	sCD14, CRP, AGP, KT ratio
Epigenetic metabolomes	Blood	LRP1
Enteric infection	Faeces, breath sample	TaqMan Array Card, SIBO
Nutrient malabsorption	Blood	Ferritin, zinc, GLP-2, pepsinogen I/II ratio
Celiac Disease screening	Blood	IgA tissue transglutaminase, total IgA

AGP, alpha 1-glycoprotein; CRP, C reactive protein; KT ratio, kynurenine/tryptophan ratio; LRP1, low density lipoprotein receptor-related protein 1; GLP-2, glucagon-like peptide-2; Reg1B, regenerating family member 1 beta proteins; sCD14, soluble cluster of differentiation 14; SIBO, small intestinal bacterial overgrowth.

### Indications for and details of the procedures used for UGI tract endoscopy and mucosal biopsy

After completion of nutritional therapy, all enrolled participants are assessed for responses. Definitions of ‘failure to thrive/respond’ are as follows:LAZ score remains <−2 for members of the stunted children cohortLAZ score remains <−1 for the ‘at risk of stunting’ children cohortBMI <18.5 kg/m^2^ and <10% increase in BMI for those in the adult cohort

Participants who meet the study definition of ‘failure to thrive/respond’ are further checked for the presence of any secondary cause of malnutrition such as tuberculosis, any parasitic infection, and so on. If nothing conclusive is found, the participant may undergo preparations for UGI endoscopy with biopsy. Participants with celiac disease (as defined by tissue transglutaminase IgA, and clotting disorders (determined by prothrombin time/International normalised ratio (INR) coagulopathy tests) will be excluded from the study. There is no published information about the prevalence of celiac disease in Bangladesh from any representative sample.^16^ One study of hospitalised adult patients with irritable bowel syndrome observed that the prevalence of celiac disease was 9%.^17^ In the BEED study, immediate test results for celiac disease are not available; therefore, we are unable to screen out individuals with this disorder before nutrition intervention is initiated. Nonetheless, BEED will screen 1575 participants for celiac disease; as such, it will be the first study in Bangladesh to explore the prevalence of this disorder in a paediatric population. Necessary management and counselling is provided to the participants suffering from celiac disease or clotting disorders.

Endoscopy of the UGI tract is performed as per standards recommended by North American Society for Pediatric Gastroenterology, Hepatology and Nutrition, the American College of Gastroenterology and the American Society for Gastrointestinal Endoscopy (ASGE).^18^ The procedure is generally scheduled in the early morning after fasting from midnight. Gastroenterologists, who perform endoscopy, discuss with the subjects and their guardians regarding the indication of the procedure, the sedation plan, the risks associated with sedation and describe the total procedure, likely benefits, common adverse events (AEs), alternatives to the procedure and the prognosis of the subjects if endoscopy is declined. After this discussion and proper counselling, the gastroenterologists personally obtain consent from the subjects on the day of the procedure. A separate consent is obtained for sedation. A preprocedure assessment that includes medical history and physical examination is also completed by the gastroenterologist himself.

Once the preprocedure assessment is completed and no concerns are identified by the gastroenterologist, the subject is proceeded to the endoscopy room. A qualified anaesthetist attends the procedure to assess and administer the steps, as required, for sedation. Before sedation is administered, the intended level of sedation is graded (nil, minimal, moderate and deep sedation or general anaesthesia) as per the recent guidelines of ASGE.^18 19^ Children are sedated using general anaesthesia by an expert and qualified anaesthetist. UGI endoscopies of adult participants are performed under conscious sedation using midazolam. The oropharynx is anaesthetised with 10% lidocaine spray; concomitantly, midazolam (3–5 mg) is injected intravenously to induce conscious sedation.^19^

The endoscopic procedure is performed with a goal of collecting up to six biopsies from each child and up to eight biopsy samples from each adult participant. As per the protocol, one biopsy is taken from the duodenal bulb; the rest of the biopsies are collected from the distal part of the duodenum. Duodenal fluid is aspirated for culture-independent and culture-based assessments of the composition of the proximal small intestinal microbial community and for assays of host and microbial products. Secretions are rapidly aspirated first from the second portion of the duodenum using sterile Endoscopic Retrograde Cholangiopancreatography (ERCP) catheters. Following this initial aspiration, the postbulbar mucosa is irrigated with a maximum of 25 mL of sterile 0.9% normal saline, and the lumen contents are aspirated through the ERCP catheter. The lavaged aspirates are aliquoted and processed as per the SOP described in table 3.

**Table 3 T3:** Biopsy specimen processing

Specimen	Recipient fluid	Processing	Purpose
Biopsy #1	RNAlater	Nucleic acid extraction	Transcriptomics
Biopsy #2	HBSS	FACS	Cell isolation
Biopsy #3	None	Flash frozen	Culture-independent and culture-based assays of mucosa-associated microbial community
Biopsy #4	None	Flash frozen	Archiving for validation of drug targets
Biopsies #5 and #6*	Formalin	Paraffin embedded	Histochemistry (H&E) and immunohistochemistry; Morphometric analyses and EED scoring
Duodenal Aspirate	Microbiota: glycerol/cysteine solution Other: Nil	Precharged N_2_ dry shipper to −80 freezer	Culture-independent and culture-based assays

*Biopsy site: biopsy #6 from duodenal bulb, all others distal to the ampulla of Vater.

EED, environmental enteric dysfunction; FACS, fluorescence-activated cell sorting; HBSS, Hank’s balanced salt solution.

Participant undergoing endoscopy is observed in the postprocedure recovery room until he/she meets predetermined standard discharge criteria.^20^ The subjects who undergo the endoscopy procedure are followed up for 14 days after the procedure to determine whether any AEs have occurred after discharging from the endoscopy unit and whether these are attributable to the procedure. An appropriate course of action will be followed if such events occur; the cost of management of all postprocedure complications will be borne by the study. Participants receive appropriate treatment based on the results of reports from the endoscopy and biopsy procedure. As for example, participants diagnosed endoscopically with antral gastritis are screened for *Helicobacter pylori* and prescribed proper treatment, as per standard recommendations.

### Protocol timeline

The overall schedule for enrolment, interventions and assessments, including UGI endoscopy and biopsies, is described in table 4.

**Table 4 T4:** Schedule of enrolment, interventions and assessments

	Study period							
	Enrolment	Preintervention	Nutrition intervention			Postintervention assessment	Eligibility assessment for UGI endoscopy	UGI endoscopy and biopsy
Timepoint	***−T_1_***	0	Month 1 (***T_1_***)	Month 2 (***T_2_***)	Month 3 (***T_3_***)	Week 1 (***T_4_***)	Week 2 (***T_5_***)	Week 3 (***T_6_***)
Enrolment	X							
Pre-enrolment survey	X							
Eligibility screen	X							
Informed consent	X						X	
Interventions								
Stunted children								
Children at risk of stunting								
Malnourished adult								
Assessments								
SES, WASH, FFQ		X				X		
Anthropometry*		X	X	X	X	X		
Blood biomarkers		X				X		
Stool biomarkers and TAC		X				X		
Microbiota		X				X		
Urine L:R		X				X		
Breath SIBO		X				X		
UGI endoscopy and biopsy		X				X		
Histopathology, IHC, morphometry								X

*Anthropometry done fortnightly.

IHC, immunohistochemistry; L:R, lactulose/rhamnose; SIBO, small intestinal bacterial overgrowth; TAC, TaqMan Array Card; UGI, upper gastrointestinal; SES, socio-economic status; WASH, water-sanitation-hygiene; FFQ, food frequency questionnaire.

### Data collection, management and storage

Data collection tools for this study include case report forms, laboratory worksheets and source documentation. Complete source documentation (study visits, laboratory reports, and so on) is done for each participant in individual study charts. All laboratory specimens, reports, study data collection and administrative forms are identified by coded number to maintain participant confidentiality and to enable tracking throughout the study. Bar-coded labels are used for all laboratory specimens. All information regarding study subjects are kept in password-protected computer files, or in locked file cabinets that can be accessed only by authorised study personnel. Anthropometric data (table 4) are collected twice in a month. The total amounts of food offered, consumed and leftover are recorded. All foods are weighed with precision scales (see online supplementary file 3). Multiple food frequency data are collected from all the participants, whereas a 24 hours dietary recall data are being collected from a subgroup of randomly selected children as well as adults (50 in each group) to assess their food habits and food substitution, if any.

### Data analysis plan

This study will yield a rich dataset containing socio-demographic and anthropometric information, food security status, plus faecal, urine, plasma and breath associated biomarkers, the results of histopathological measurements as well as data related to small intestinal gut health risk factors. After evaluation of biopsy specimens, a pathologist will assign a histopathological grade, in a blinded fashion, based on histological changes deemed to be signatures of EED: these include changes in mucosal architecture (shortening of the villi, increase in the depth of the crypts), changes in immune-inflammatory cell content (lymphocytic infiltration into the lamina propria and epithelium) and changes in epithelial features (goblet cell content, evidence of enterocyte injury and so on).^21^ Statistical tests of correlations between histopathological scores, biomarker levels and anthropometric changes will be performed. An ‘inter-group’ comparison (stunted children vs children at risk of stunting; stunted vs non-stunted, and so on) will be performed for validation of histopathological grading. The analysis plan includes relatively simple linear modelling of all continuous and dichotomous measures to establish whether biomarkers are associated with anthropological changes or not. Biomarkers exhibiting statistically significant changes will be identified and their final validation will be performed by comparing their levels with histopathological changes.

An important research question is whether enteric infections, and gut immune responses to those infections, are associated. While preliminary inferences of linkage are possible from a careful interpretation of simple univariate and bivariate analyses, instrumental variable analysis (for the control of unmeasured covariates) will also be performed.

Being an invasive procedure requiring hospitalisation, histopathological diagnosis of EED will not be possible as a routine approach in at-risk populations in low-income settings. A goal of this project is to validate surrogate biomarkers of the disease and use these for developing models to predict future negative histopathological and clinical outcomes. From a list of significant biomarker variables, we will select a ‘best’ subset by using a branch and bound algorithm. This method will test all biomarker subsets in contrast to the more usual forward or reverse stepwise regression. As development of prediction model risks over-fitting to the data set, we plan to partition the data set into model training (2/3) and test (1/3) subsets, using the test set at the end of the fitting to establish an unbiased estimate of the generalisation error. We will estimate the prediction error in the training set using cross-validation methods. A subset model of biomarkers will also be used to create a composite score of EED.

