### Objectives

The goals of this study are to (1) develop a histological scoring system for identifying EED and describing its severity; (2) employ this scoring system to test the validity of proposed, candidate non-invasive biomarkers of EED and identify novel biomarkers; (3) test the degree of correlation between EED score and nutritional status defined by anthropometry; (4) determine the role of the gut microbiota in the pathogenesis of EED, in part through transplantation of luminal/mucosal proximal small intestinal and faecal microbiota from malnourished children with and without histopathological evidence of EED into gnotobiotic mice to directly test transmissibility of gut barrier/mucosal immune, growth and metabolic phenotypes and (5) characterise biological pathways that operate in the host and/or gut microbiota that are associated with EED to identify potential therapeutic targets.

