**Figure 1 F1:**
[figure not shown]
Study design of Bangladesh Environmental Enteric Dysfunction study. GI, gastrointestinal.

The BEED study is recruiting two control groups in order to compare the histological features in their duodenal mucosal biopsies with those of documented in cases of EED. Due to obvious ethical considerations, it is not possible to collect small intestinal biopsy samples from entirely healthy and asymptomatic subjects. Therefore, biopsies are being collected from children who are neither stunted nor suffering from EED and who undergo upper gastrointestinal (UGI) endoscopy as part of their clinical care. This control group of children are being recruited by the collaborators at the University of Virginia Hospital in Charlottesville, Virginia, USA. An equal number of age-matched and sex-matched healthy adult controls (BMI >18.5) suffering from functional dyspepsia who have no evidence of any organic diseases are being recruited from the Gastroenterology Outpatient Department of DMCH and the icddr,b Staff Clinic and undergo UGI endoscopy.

Following application of the inclusion/exclusion criteria listed in online supplementary file 1, undernourished children and adults are receiving nutrition and health interventions (table 1). Participants who fail to respond to nutritional therapy are considered eligible for UGI endoscopy with mucosal biopsies. Candidate EED biomarkers are being measured in faeces, urine and plasma samples collected from participants once before and once after the nutritional intervention.

10.1136/bmjopen-2017-017768.supp1Supplementary data

**Table 1 T1:** Nutrition and health interventions

Intervention	Delivery method
Egg	One egg daily, 6 days a week for either 2 months (children at risk for stunting and malnourished adults) or 3 months (stunted children)
Milk	150 mL whole milk daily, 6 days a week for either 2 months (children at risk for stunting and malnourished adults) or 3 months (stunted children)
Micronutrient sprinkles	–Parents will be given one sachet of multiple micronutrient sprinkles per day to be administered to the child at home with the midday meal for 2 months –Each sachet contains one recommended dietary allowance (RDA) of vitamin A, vitamin C, folic acid, iron and zinc

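### Final validation of a biomarker against histology is made conditional on a significant change or growth association, which is the wrong filter for objective 2 and conflicts with the unfiltered correlations planned elsewhere

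*Protocol article*

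**What the plan says.** Objective 2 is to "employ this scoring system to test the validity of proposed, candidate non-invasive biomarkers of EED". The yardstick is therefore the histology score.

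The Data analysis plan contains three statements on how biomarkers meet histology:

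- Early in its first paragraph: "Statistical tests of correlations between histopathological scores, biomarker levels and anthropometric changes will be performed". No filter is attached.
- Later in that paragraph it plans "relatively simple linear modelling of all continuous and dichotomous measures to establish whether biomarkers are associated with anthropological changes or not", and follows this with: "Biomarkers exhibiting statistically significant changes will be identified and their final validation will be performed by comparing their levels with histopathological changes".
- In the paragraph on prediction models: "From a list of significant biomarker variables, we will select a ‘best’ subset by using a branch and bound algorithm". A subset model is then also used for a composite EED score.

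The Methods and analysis part of the abstract says that the candidate biomarkers will be correlated with nutritional status and with the tissue analyses, again without a filter.

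On the intervention side, Table 1 describes daily sachets for the children: "Each sachet contains one recommended dietary allowance (RDA) of vitamin A, vitamin C, folic acid, iron and zinc". Table 2 lists, under nutrient malabsorption, "Ferritin, zinc, GLP-2, pepsinogen I/II ratio".

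**The concern.** Agreement with histology is one relation; movement during 2 to 3 months of feeding, or association with growth over that time, is another. A marker of persistent mucosal damage need not move. This matters most in the intervention participants who are biopsied, because they qualify for endoscopy by failing to respond. A stable, abnormal marker is quite plausible there, and it is the kind of marker objective 2 should find.

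The screen can also err in the other direction. A marker moved by the supplement itself can pass with no link to the mucosa. Zinc and ferritin in children are the evident cases.

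If the condition is applied as worded, a good marker may miss final validation, the prediction model and the composite score, for a reason unrelated to whether it reflects the tissue.

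**Working it through.** **Inputs from the article.** 525 recruited per cohort and 35 biopsied per cohort, 105 in all (Sample size). One biomarker sample before and one after the intervention (Study settings and participants). 17 candidates in Table 2, by my count, leaving out the two celiac tests and counting the TaqMan Array Card and SIBO as one each.

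**Assumptions.** The article gives no significance level for the screen; I take 0.05 two-sided. All true changes and correlations below are assumed.

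**The plan's own figures.** n = 1.96² × 0.9 × 0.1 / 0.1² = 34.57, rounded up to 35. Then 35 × 3 = 105 per cohort before consent to endoscopy, and 105 / 0.20 = 525 recruited per cohort. These reproduce. They concern the precision of a proportion and say nothing about the screen.

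**Step 1: passing the screen if it is on pre/post change.** With a true mean change of d SD (SD of the paired differences), P(pass) ≈ Φ(d√n − 1.96) + Φ(−d√n − 1.96), n = 525, √525 = 22.91.

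| True change d | P(pass) in one cohort |
|---|---|
| 0 | 5% |
| 0.05 | 21% |
| 0.10 | 63% |
| 0.20 | 99.6% |

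If passing in any one of the three cohorts is enough, the null figure is 1 − 0.95³ = 14%.

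**Step 2: passing the screen if it is on association with growth.** By the Fisher z approximation, P(pass) ≈ Φ(atanh(r)√(n−3) − 1.96), plus a negligible second tail unless r is near 0. For r = 0 it is 5%. For r = 0.1 at n = 525: 0.1003 × √522 = 2.29, and Φ(0.33) = 63%. The two readings of the sentence give similar answers.

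**Step 3: the direct test against histology.** Same formula, for the correlation of marker and histology score. For r = 0.5 at n = 105: 0.5493 × √102 = 5.55, and Φ(3.59) is above 99.9%. Two cohort terms change 102 to 100, giving Φ(3.53), still above 99.9%.

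| True r with histology | Level | n = 35 | n = 70 (children) | n = 105 |
|---|---|---|---|---|
| 0.5 | 0.05 | 87% | 99% | >99.9% |
| 0.5 | 0.05/17 | 55% | 94% | 99.5% |
| 0.3 | 0.05 | 42% | 72% | 88% |
| 0.3 | 0.05/17 | 11% | 33% | 56% |

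**Step 4: both in sequence.** For a marker with d = 0 and r = 0.5, treating the two results as independent, passing the screen in its cohort and then succeeding against histology at n = 105 has probability 0.05 × 0.999 ≈ 5%, against more than 99.9% without the screen. With d = 0.10 it is 63%.

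**Step 5: supplemented nutrients.** The pre/post screen has 80% power at d = (1.96 + 0.84)/22.91 = 0.12 SD. A small rise in zinc or ferritin would therefore usually pass. Whether a rise of that size occurs cannot be worked out from the article.

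**The case against.** The strongest reply is that the direct comparison is already planned. The unfiltered correlations in the Data analysis plan and the abstract cover the candidates against histology, so a marker that fails the screen loses its final validation, and perhaps entry to the model, but not necessarily every look at histology. This stands. A reader might infer that only screened markers are ever compared with histology and that the rest are discarded; the article does not say so.

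A reader might also infer that the screen runs without multiplicity control. With 17 independent null markers at 5%, the chance of at least one false pass would be 1 − 0.95¹⁷ = 58% per cohort. But the article is merely silent, and such a rule may sit in an analysis plan that is not shown. A chance pass must also still face histology, and the prediction model has cross-validation and a held-out third. I place no weight on the 58%.

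Other replies hold in part. The 5% applies only when the true change or growth association is zero. The list of significant variables for the model might mean significant against histology. The prediction aim includes clinical outcomes, so relevance to growth is a fair question, though a separate one. The supplementation point touches 2 of 17 markers, in children only, and a response to supplied nutrients may itself be informative about absorption.

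None of this removes the sentence that ties final validation to prior significance, or settles which of the two routes decides that a marker is valid.

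**Conclusion.** The point holds in limited form. The Data analysis plan makes final validation conditional on a significant change or growth association, carries an undefined list of significant markers into the model and the composite score, and plans unfiltered correlations with histology alongside. The filter tests a relation that objective 2 does not ask about, and the statements need to be reconciled.

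Size: at an assumed two-sided 0.05, a marker with no true change or growth association passes in a cohort about 5% of the time whatever its relation to histology, while a direct test at n = 105 would detect a true correlation of 0.5 more than 99% of the time. The loss shrinks quickly as the true change grows and is nearly gone at 0.20 SD. The tilt towards zinc and ferritin in children is a plausible risk of unknown size.

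**What to change.** - Remove the condition on significant change. Compare all prespecified Table 2 candidates directly with the histology score in all biopsied participants, adjusted for cohort, with a stated error control such as Benjamini-Hochberg over the list. Name this as the analysis that decides validity.
- Report pre/post change and association with growth as separate secondary analyses.
- Start the branch-and-bound selection from the full candidate list, or from association with histology assessed within the training set only, and say which.
- For zinc and ferritin, an analysis using pre-intervention values, or adjusting for CRP and AGP, could be offered at most as a sensitivity analysis. The pre-intervention sample precedes the biopsy by months, and CRP and AGP are themselves candidate markers, so adjusting for them could remove disease signal.

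Cost: analysis wording only, with no new assays or participants. Single-marker claims become somewhat harder. The Bonferroni rows above give a floor, since Benjamini-Hochberg at the same level rejects at least as much: for r = 0.5, power is still at least 94% at n = 70 and 99.5% at n = 105, but for r = 0.3 the floor falls to 33% and 56%.

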### Sample size

Participants are being recruited in a cross-sectional manner. Sample size calculations were predicted on the following assumptions: prevalence of stunting at our study site is 40%; after receiving nutrition intervention ~20% will fail to manifest improved linear growth; only one-third will give their consent for endoscopy and 90% of the stunted children will have one or more abnormal gut biomarkers with a precision of 10% and 95% CI. Using the formula n=(Z_1−α/2_)^2^×P×(1−P)/d^2^, where n is the required sample size without attrition; P is the prevalence of one or more abnormal gut biomarker in stunted children=90% or 0.9; d is the level of actual precision=10% or 0.1; Z_1−α/2_ is the value for standard normal distribution at 95% level of significance=1.96, a minimum of 35 stunted children, 35 children at risk of stunting and 35 malnourished adults will be needed for UGI endoscopy and biopsy. Therefore, the final sample size for endoscopy is 105 subjects (35+35+35). As endoscopy is an invasive procedure, we assume that only one-third of those who will fail to respond after nutrition intervention will give consent for the procedure. As a consequence, the ‘basic’ sample size was increased threefold for a minimum of 105 (35×3) stunted children, 105 (35×3) children at risk of stunting and 105 (35×3) malnourished adults. To achieve this goal, 525 stunted children, 525 children at risk of stunting and 525 malnourished adults will be recruited for nutrition interventions, based on the assumption that ~20% of each group will fail to respond despite the nutritional intervention. To enrol the desired numbers of participants, at least 3977 (1312+2665) children 12–18 months old and 2100 adults needed to be surveyed based on the current prevalence of malnutrition in both the age groups. An equal number (35) of age-matched and sex-matched apparently healthy adult controls (BMI >18.5) will be recruited from the outpatient department of DMCH and icddr,b Staff Clinic. Apart from the dyspeptic symptoms by Rome III criteria,^7^ these subjects will have no other symptoms.

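### The significance screen is not confined to the training data as written, so the test third is not assured to give the unbiased error estimate the plan promises

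*Protocol article*

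**What the plan says.** The Data analysis plan describes two stages.

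The first stage consists of correlation tests among histopathological scores, biomarker levels and anthropometric changes, together with linear models "to establish whether biomarkers are associated with anthropological changes or not". It ends with this sentence: "Biomarkers exhibiting statistically significant changes will be identified and their final validation will be performed by comparing their levels with histopathological changes". No training subset is mentioned anywhere in this stage.

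The second stage builds a prediction model: "From a list of significant biomarker variables, we will select a ‘best’ subset by using a branch and bound algorithm". The text then raises over-fitting and answers it with a partition: "we plan to partition the data set into model training (2/3) and test (1/3) subsets". Prediction error in the training set is to be estimated by cross-validation, and the held-out part is reserved for "using the test set at the end of the fitting to establish an unbiased estimate of the generalisation error". A subset model is also to supply a composite EED score.

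On numbers, the Sample size section states that "the final sample size for endoscopy is 105 subjects", or 35 in each of three cohorts. The size of the test set is not stated.

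**The concern.** A held-out set gives an unbiased error estimate only if its subjects played no part in building the model, and choosing the candidate predictors is part of building it. The partition is offered as protection for the model fitting. Nothing extends it back to the significance analyses that supply the fitting's input. Read naturally, all subjects contribute to the shortlist and a third of them are then used to judge it. A biomarker that passes the screen by chance does so partly because of chance associations among the test subjects, and those associations reappear as apparent predictive skill.

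Objective 2 of the study is to test candidate non-invasive biomarkers against the histological score. A held-out result that is too favourable would lend that validation, and the composite score, support they have not earned.

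**Working it through.** **Inputs from the protocol article.** P = 0.9, d = 0.1, Z = 1.96, 35 biopsies per cohort and 525 recruits per cohort (Sample size). A 2/3 to 1/3 split (Data analysis plan). 17 candidate biomarkers, counted from Table 2 without the two celiac tests and with the TaqMan Array Card counted once.

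**Assumptions, not in the document.** Two-sided p<0.05 for the screen. Best subset chosen by BIC from at most six shortlisted biomarkers, with at least one retained. Independent normal biomarkers and a linear model.

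**1. The plan's own figure.** n = Z²P(1−P)/d² = 1.96² × 0.9 × 0.1 / 0.01 = 34.57, rounded up to 35. Then 35 × 3 = 105 biopsies. The figure reproduces.

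**2. Size of the split.** For a histology model on the 105 planned biopsies: 105 × 2/3 = 70 training and 105/3 = 35 test subjects. For a clinical outcome measured in all recruits: 525 × 3 = 1575, so up to 1575/3 = 525 test subjects.

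**3. Bias when the screen uses all 105 subjects and the modelled outcome.** There were 3,000 simulated data sets per setting. Results are for runs in which at least one biomarker passed the screen. With 17 null biomarkers this was 57–58% of runs, in line with 1 − 0.95¹⁷ = 0.58.

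| Setting | Screen on | Mean test correlation | Test MSE | True MSE |
|---|---|---|---|---|
| 17 biomarkers, none predictive | all 105 | 0.205 | 0.999 | 1.090 |
| 17 biomarkers, none predictive | 70 training | −0.004 | 1.128 | 1.122 |
| 17 biomarkers, 3 predictive (slope 0.25) | all 105 | 0.298 | 1.116 | 1.164 |
| 17 biomarkers, 3 predictive (slope 0.25) | 70 training | 0.220 | 1.187 | 1.187 |

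Relative understatement of error with the screen on all subjects:
- no predictive biomarkers: (1.090 − 0.999)/1.090 = 8%;
- three predictive biomarkers: (1.164 − 1.116)/1.164 = 4%.

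Confining the screen to the training subjects removes the bias in both settings.

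**4. Bias when the screen uses a different outcome.** With 17 null biomarkers screened on all 105 subjects against a second outcome, the mean difference between test and true MSE was −0.007 (SE 0.006) when that outcome correlated 0.3 with the modelled one. It was +0.010 (SE 0.006) at correlation 0. Both are negligible.

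**5. Two-stage screen.** Suppose 8 of the 17 biomarkers pass a first stage on anthropometry, all are null for histology, and a histology screen at p<0.05 follows on all 105. Mean test correlation is 0.21, against 0.00 when the histology screen is kept within the 70. A preceding anthropometric stage therefore does not remove the problem.

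**6. Precision at 35 test subjects, a separate matter from bias.** For r = 0.5: atanh(0.5) = 0.549; half-width 1.96/√(35 − 3) = 0.346; limits tanh(0.203) = 0.20 and tanh(0.896) = 0.71.

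**The case against.** The strongest reply is that no sentence places the screen before the split. The paragraph is not in strict time order, since cross-validation in the training set is mentioned after the final use of the test set. Branch and bound is also described before the partition, yet it is presumably meant for the training part. The investigators may intend the screen to be confined in the same way. This stands. A reader might infer that the test set cannot be unbiased, and the document does not support so strong a claim. It supports only that the stated property is not assured by the procedure as described.

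Second, the sentence about significant changes follows directly on models for anthropometric change. If that alone forms the shortlist, and it tracks histology weakly, the bias is negligible (step 4). This also stands. However, the same section tests biomarkers against histopathological scores and calls the comparison with histopathology the final validation, so a histology filter on the list is a plausible reading.

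Third, the size depends on unstated choices. If the criterion may return an empty model, the mean null test correlation falls to 0.13, and a nominally significant test result occurs in 2.4% of all runs, about the nominal 2.5%. With 1575 subjects the mean correlation is only about 0.05–0.06. The 8% is therefore illustrative and conditional.

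Fourth, 35 test subjects should not be read as applying to every model. A clinical-outcome model could hold out up to 525. Biopsied controls exist as well, and the text does not say whether they enter the model. Nor does it plan a separate split per cohort. Finally, a small test set makes an estimate imprecise but does not contradict the claim that it is unbiased.

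**Conclusion.** The point holds in a limited form. The plan claims a specific property for its test-set error and describes a procedure that does not secure it. On the natural reading, subjects in the test third help to pick the predictors. If the list is filtered on all subjects against the modelled outcome, error in a 105-subject histology model is understated by about 8% when no biomarker is predictive and by about 4% when three are, under the assumed threshold and selection rule. If the filter is only a weakly related outcome, there is essentially no bias.

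This concerns a property the plan asserts, not detail it was free to leave to a fuller document. That the composite score would be worthless, or would falsely pass validation, does not follow from the text. Separately, about 35 test subjects give a wide interval for a histology model even when the estimate is unbiased.

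**What to change.** State that the split is made before any outcome-based screening, and that the significance screen, the branch-and-bound search and the composite-score weighting use the training data only. Alternatively, put the whole sequence inside nested cross-validation or bootstrap optimism correction. If neither is done, delete the word unbiased. In either case, report a confidence interval for test-set performance and the number of subjects behind it.

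The cost is one paragraph and some analysis code, and no extra data are needed. The downside is that reported performance will look less favourable. Moving the screen into the training data also does nothing for precision, because the histology test set stays at about 35 if the single split is kept.
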